## Abstract

(1) Background: Previous school-based interventions have addressed adolescent health behaviors such as physical activity, screen time, and sleep, but have predominantly targeted these behaviors independently rather than simultaneously. The Erasmus+ project FiTeens developed an integrated intervention combining theoretical content, videos, infographics, and interactive tasks to promote multiple health behaviors concurrently. The objective of the current article is to present the protocol for a school-based intervention study designed to examine the effects of the FiTeens program on adolescents’ physical activity, screen time, and sleep behaviors. We hypothesize that students receiving the FiTeens intervention will demonstrate increased physical activity, reduced screen time, and improved sleep outcomes compared with students in the control group. (2) Methods: Teachers will be introduced to the FiTeens tools prior to delivering the intervention to students in grades 5–9. Students will participate in an eight-week intervention program combining structured lessons and behavior-change challenges. Primary outcomes include changes in physical activity, screen time, and sleep duration and quality. Secondary outcomes include psychological determinants such as motivation and behavioral intentions. Data will be collected at baseline and at 1-, 3-, and 6-month follow-ups and analyzed using repeated measures ANOVA. (3) Expected results: The study will evaluate whether the intervention may contribute to improvements in health-related behaviors among adolescents, including increased physical activity, reduced screen time, and improved sleep outcomes. (4) Conclusions: The intervention based on FiTeens tools could have the potential to promote healthier lifestyle behaviors among students by increasing physical activity during leisure time, supporting the effective limitation of screen time and enhancing bedtime routines to improve sleep quality.

## 1. Introduction

Physical inactivity, excessive screen time, and insufficient sleep are common health concerns among adolescents and are associated with adverse physical and psychological outcomes [1,2,3,4,5,6,7,8]. These health behaviors are closely interrelated and represent important targets for school-based health promotion initiatives.

Problems associated with low physical activity, excessive screen time, and insufficient sleep can be addressed through various intervention programs [9]. A meta-analysis Indicated that the most effective interventions were school-based and multifaceted, incorporating different physical activities. Shorter interventions lasting 12–26 weeks appeared somewhat more effective than longer interventions (>26 weeks) [10]. Previous research has also highlighted the importance of involving teachers and parents in intervention delivery, consistent with the Creating Active Schools framework, which emphasizes the promotion of healthy lifestyles through the entire school community [11]. Although some interventions have focused on screen time reduction, many have primarily targeted dietary behaviors, with only limited emphasis on physical activity and other related health behaviors [12].

The current study is based on the Erasmus+ project “FiTeens: Promoting Physical Activity and Healthy Lifestyles among Sedentary Youth”, which developed a set of digital educational resources, including an e-book, a MOOC platform, and web-based health behavior challenges designed to promote healthy lifestyle behaviors among adolescents [13]. Unlike many previous interventions, the FiTeens program simultaneously targets physical activity, screen time, and sleep through a structured school-based approach combining teacher-led lessons, digital learning materials, and behavioral challenges. Furthermore, the intervention is grounded in Self-Determination Theory and the Theory of Planned Behavior, aiming to support motivation, behavioral intentions, and sustainable behavior change across multiple health behaviors simultaneously. By integrating digital resources directly into the educational process, the FiTeens intervention may provide a more comprehensive and ecologically valid approach for promoting healthy lifestyles among adolescents within real-world school settings.

The aim of the present protocol article is to describe the design, intervention procedures, outcome measures, and planned evaluation of a school-based FiTeens intervention designed to promote physical activity, reduce screen time, and improve sleep among adolescents.

## 2. Materials and Methods

### 2.1. Study Design

The study is designed as a quasi-experimental study with school-level allocation, involving one intervention school and one control school. Due to practical constraints in the school setting, randomization at the individual or school level was not feasible. This approach was chosen to minimize contamination between participants within the same school. As a result, potential school-level differences may influence the observed outcomes. To address this limitation, baseline characteristics will be compared between groups and considered when interpreting the findings. Nevertheless, residual confounding due to contextual differences between schools cannot be entirely ruled out. Therefore, caution should be exercised when generalizing the findings beyond the participating schools.

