### 2.2. Participants

Participants of this study will be students from grades 5 to 9 (ages 11–15) recruited from general education schools in Estonia, with one school designated as the intervention group and one school designated as the control group.

Sample size estimation was conducted using G*Power 3.1 based on a repeated measures ANOVA design with two groups and four measurement occasions. Assuming a medium effect size (f = 0.25), an alpha level of 0.05, and a statistical power of 0.80, a minimum sample size of 128 participants was required (64 participants per group). To account for potential participant attrition during follow-up assessments, the target sample size was increased by approximately 40–50%. Dropout rates of 20–40% have been reported in previous school-based interventions involving adolescents, which informed the decision to increase the sample size [14].

Participants in the control group will continue with their regular school curriculum and will not receive the FiTeens intervention during the study period.

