#### 2.4.2. Intervention Phase

During the intervention phase, students will participate in an 8-week school-based program consisting of weekly teacher-led lessons supported by the FiTeens educational resources. Each lesson will last 90 min and follow a standardized structure including an introduction, main activity, and conclusion. Students will receive a learning portfolio focusing on physical activity, screen time, and sleep, and will complete weekly home-based challenges available through the FiTeens platform. Challenge completion and reflections will be documented using a challenge diary and discussed during subsequent lessons. The intervention incorporates behavior change techniques such as goal setting, self-monitoring, guided reflection, and group discussion. An overview of the intervention content is presented in Figure 2.

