### 2.6. Statistical Analysis

All statistical analyses will be conducted using IBM SPSS Statistics for Windows, Version 29.0 (IBM Corp., Armonk, NY, USA) and JASP, Version 0.17.1 (JASP Team, Amsterdam, The Netherlands). Descriptive statistics will be calculated for all study variables. The primary statistical analysis will be performed using repeated measures ANOVA, which was selected because it is appropriate for evaluating within-subject changes across repeated measurement occasions and between-group differences over time in the present study. The analysis will examine the main effects of group and time, as well as the group × time interaction effect for physical activity, screen time, and sleep-related outcomes across four measurement points (baseline, 1-, 3-, and 6-month follow-up assessments). Baseline measurements will be included in the repeated measures design to evaluate changes over time within and between groups. Independent samples *t*-tests will additionally be used to examine baseline differences between the intervention and control group, as well as differences between study completers and dropouts at baseline. As schools are allocated to intervention and control conditions at the school level, baseline differences between groups will be examined prior to the main analyses and considered when interpreting the findings. Potential school-level effects and residual confounding cannot be completely excluded and should therefore be considered when interpreting the study findings. Prior to the main analyses, data will be screened for missing values, and the extent and pattern of missingness will be examined and reported. Missing data will be addressed using multiple imputation procedures prior to analysis. An intention-to-treat approach will be applied, including all participants as originally allocated to their groups. Dropout rates and reasons for attrition will be reported and examined. Potential confounding variables, such as age and gender, will be considered where appropriate.

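### The primary repeated measures ANOVA treats students as independent although whole schools are allocated, one per arm; its standard errors omit clustering and school-specific change, which cannot be estimated here.

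*Protocol article*

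**What the plan says.** Section 2.1 calls the design a "quasi-experimental study with school-level allocation", "involving one intervention school and one control school", and explains that "randomization at the individual or school level was not feasible". Section 2.4.2 describes an "8-week school-based program consisting of weekly teacher-led lessons", and section 2.4 adds that sessions include group discussion.

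Section 2.6 states: "The primary statistical analysis will be performed using repeated measures ANOVA". It justifies this method as suitable for between-group differences over time, and continues: "The analysis will examine the main effects of group and time, as well as the group × time interaction effect". Baseline is one of the four occasions. No school, class, teacher or grade term is named. Age and gender are to be considered where appropriate.

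The sample size in section 2.2 is "based on a repeated measures ANOVA design with two groups and four measurement occasions", with f = 0.25, alpha 0.05 and power 0.80, giving 128 students (64 per group), then raised by about 40–50% for attrition. It contains no ICC or design effect.

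Sections 2.1 and 2.6 both acknowledge that school differences and residual confounding may affect the results. The responses are a baseline comparison and caution in interpretation. The Abstract nevertheless describes a study "designed to examine the effects of the FiTeens program on" the three behaviors.

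**The concern.** The unit of allocation is the school and the unit of analysis is the student. Students in one school share teachers, sessions, timetable and local events. An ordinary repeated measures ANOVA takes its error from variation among students only and treats each student as separate information.

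Two things follow. First, correlation among students taught together is left out of the standard errors. Second, whatever happens in one school and not in the other during follow-up falls on the same contrast as the program. At stake is whether an ordinary difference between two schools could reach p < 0.05 and be reported as an effect of FiTeens on a primary outcome.

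**Working it through.** **1. The plan's own figure.** Inputs from section 2.2: f = 0.25, two groups, alpha 0.05, power 0.80. For a two-group test on independent students at one occasion, λ = f²N = 0.0625 × 128 = 8, with 1 and 126 degrees of freedom. Power is 0.801, so 128 reproduces. The calculation assumes independent students throughout.

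**2. School-level degrees of freedom.** 2 schools − 2 arms = 0. No between-school error term can be estimated from these data, whatever the model.

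**3. What each planned test absorbs.**

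| Source of variation | Group main effect | Group × time |
|---|---|---|
| Stable school or class difference | included | cancels, because baseline is an occasion |
| School-specific change over time | included | included, aliased with the program |
| Class-specific change over time | included | included |

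**4. Size for a single comparison of means.** The article gives no ICC, so a range is assumed. Design effect (DEFF) = 1 + (m − 1) × ICC. Actual two-sided type I error of a nominal 5% test = 2 × [1 − Φ(1.96/√DEFF)].

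Example, m = 64 and ICC = 0.02: DEFF = 1 + 63 × 0.02 = 2.26; √2.26 = 1.503; 1.96/1.503 = 1.304; type I error 19%.

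The attrition increase gives 128 × 1.4 = 179 to 128 × 1.5 = 192 students, or about 90 to 96 per school.

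| Assumed ICC | DEFF, m = 64 | Type I, m = 64 | Type I, m = 90 | Type I, m = 96 |
|---|---|---|---|---|
| 0.01 | 1.63 | 12% | 15% | 16% |
| 0.02 | 2.26 | 19% | 24% | 25% |
| 0.05 | 4.15 | 34% | 40% | 41% |

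A slightly different calculation, in which the naive variance contains only the within-school part, gives 12.7%, 19.7% and 34.8% for m = 64, and 16.3%, 25.5% and 42.6% for m = 96.

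**5. Class clustering alone.** Class size is not stated; 20 is assumed. ICC 0.02: DEFF = 1 + 19 × 0.02 = 1.38, effective N = 128/1.38 = 93, type I error 9.5%. ICC 0.05: DEFF = 1.95, effective N = 128/1.95 = 66, type I error 16%. This too is for a single comparison of means.

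**6. Group × time.** The relevant quantity is the school-by-time share s of total variance, not the ordinary ICC. Assume a within-student correlation ρ = 0.5 and school-by-time effects independent across occasions. The variance of the contrast then exceeds the naive one by 1 + ns/(1 − ρ − s). For n = 64 and s = 0.01 this is 1 + 0.64/0.49 = 2.31. Simulation of the planned F test (4,000 runs, 64 per school) gave:

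| Assumed s | Variance ratio | Interval should be wider by (√ratio) | Type I error |
|---|---|---|---|
| 0 | 1.00 | 1.00 | 5.2% |
| 0.005 | 1.65 | 1.28 | 19.6% |
| 0.01 | 2.31 | 1.52 | 33.6% |
| 0.02 | 3.67 | 1.91 | 54.6% |

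The documents give no basis for choosing a row.

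**The case against.** **The confounding is already disclosed.** This stands. Sections 2.1 and 2.6 say that school differences may influence the outcomes, and section 2.1 urges caution in generalising. A reader might infer that the plan hides the problem; it does not. What it leaves unsaid is that students are correlated and that the ANOVA standard errors ignore this. Comparing baselines cannot correct a standard error or detect divergence after baseline.

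**The F tests do more than compare two schools.** A reader might infer that every test merely asks whether the schools differ. For group × time that goes too far, because stable differences cancel and only school-specific change remains aliased.

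**The size is unknown.** This also stands. A reader might infer that type I error is well above 5% for every primary outcome. The documents do not support that: they give no ICC, the 12/19/34% figures are for a single comparison of means, and the group × time error is nominal when the school-by-time variance is zero. Only the direction is secure.

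**If inference is restricted to these two schools, the school-level inflation does not apply.** Correct. In that frame the schools are fixed, and what remains is lesson-group clustering and disclosed confounding. But the article does not state that frame, and the Abstract's aim is wider.

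**A mixed model does not solve it.** It cannot supply a school-level error term with 0 degrees of freedom. It handles only within-school clustering.

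**The detail could sit in a fuller plan.** This carries little weight, because the article itself names the primary method and defends it as suitable.

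**Conclusion.** The concern holds in this limited form. The stated primary analysis takes students as independent, although allocation is by school and delivery is by group. Intervals for the group main effect are too narrow, and p-values too small, under any positive class or school clustering. The same is true of group × time under any class- or school-specific change. School-specific change cannot be separated from the program with one school per arm, nor can its variance be estimated.

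Under assumed ICCs of 0.01 to 0.05, a single comparison of means with 64 per school has a type I error of about 12% to 34%, and more with 90 to 96 per school. For group × time the size depends on an unknown school-by-time variance; the simulated figures also rest on ρ = 0.5 and independence across occasions. The documents do not support a claim that error rates are inflated by a known amount, or that they are inflated for every outcome.

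**What to change.** 1. In section 2.6, make group × time, expressed as change from baseline, the primary test in a linear mixed model. Include random effects for student and for class or lesson group (grade within school if class is not recorded), with Satterthwaite or Kenward-Roger degrees of freedom. Let the lesson-group effect vary by occasion, since a constant one cancels from change. If only grade is available there are 5 × 2 = 10 groups, so degrees of freedom may be as few as about 10 − 2 = 8.
2. State that this model handles within-school clustering only, that p-values and intervals are conditional on these two schools, and that the estimate is a difference in change between two schools which cannot by itself be attributed to the program. Align the Abstract's aim with this.
3. If any inference beyond the two schools is made, add a sensitivity table with intervals widened for assumed school-by-time ICCs, for example 0.005 to 0.05. With n = 64 and ρ = 0.5, the factor is √1.65 = 1.28 at 0.005, and √(1 + 3.2/0.45) = √8.11 = 2.85 at 0.05.

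**Cost.** Wider intervals, possibly much wider in the sensitivity table, and a weaker claim. No new schools or students are needed. Class or lesson-group membership must be recorded; the article does not say whether it is. The planned software, SPSS, has a mixed-model procedure. Separating the program from the school would need several schools per arm, which this change does not provide.

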### 2.2. Participants

Participants of this study will be students from grades 5 to 9 (ages 11–15) recruited from general education schools in Estonia, with one school designated as the intervention group and one school designated as the control group.

Sample size estimation was conducted using G*Power 3.1 based on a repeated measures ANOVA design with two groups and four measurement occasions. Assuming a medium effect size (f = 0.25), an alpha level of 0.05, and a statistical power of 0.80, a minimum sample size of 128 participants was required (64 participants per group). To account for potential participant attrition during follow-up assessments, the target sample size was increased by approximately 40–50%. Dropout rates of 20–40% have been reported in previous school-based interventions involving adolescents, which informed the decision to increase the sample size [14].

Participants in the control group will continue with their regular school curriculum and will not receive the FiTeens intervention during the study period.

### 2.3. Ethical Considerations, Consent, and Permissions

The study will be conducted in accordance with the Declaration of Helsinki and the principles of Good Clinical Practice. Ethical approval was obtained from the Research Ethics Committee of the University of Tartu (code: 1/M-6, 27 January 2026). Participation in the study is voluntary, and participants may withdraw at any time without consequences. Written informed consent will be obtained from both students and their legal representatives prior to participation. As a substantial proportion of the target population consists of non-native Estonian speakers, all study materials and consent forms will be provided in both Estonian and Russian.

### 2.4. Intervention

Prior to delivering the intervention to 5–9th grade students, teachers will first be introduced to FiTeens digital tools, including the toolkit, MOOC e-learning platform and challenges available on the FiTeens website, during 5 h intensive course. After collecting the baseline data, students will undergo an eight-week intervention program comprising lessons delivered by teachers on health-related topics combining behavior challenges provided through the FiTeens toolkit (Figure 1).

During the intervention students will undergo an eight-week program including lessons based on the content from toolkit and challenges in FiTeens website: www.fiteens.eu. Each session is based on a predefined thematic focus (physical activity, screen time, or sleep) and includes a combination of theoretical input, group discussion, and practical activities designed to promote behavior change. The study consists of pre-intervention phase, intervention phase and post-intervention phase (Figure 2).

#### 2.4.1. Pre-Intervention Phase

Prior to the implementation of the intervention program, baseline data will be collected through questionnaire administration, the use of accelerometers and Polar M400 smartwatch worn for seven consecutive days. The Polar M400 smartwatch is used as an objective measure of sleep duration. The devices are randomly distributed among students and worn on the wrist for a period of seven days. In addition, students will fill out sleep diary. Accelerometers will also be distributed, which each participant will wear on the hip for a period of seven days.

#### 2.4.2. Intervention Phase

During the intervention phase, students will participate in an 8-week school-based program consisting of weekly teacher-led lessons supported by the FiTeens educational resources. Each lesson will last 90 min and follow a standardized structure including an introduction, main activity, and conclusion. Students will receive a learning portfolio focusing on physical activity, screen time, and sleep, and will complete weekly home-based challenges available through the FiTeens platform. Challenge completion and reflections will be documented using a challenge diary and discussed during subsequent lessons. The intervention incorporates behavior change techniques such as goal setting, self-monitoring, guided reflection, and group discussion. An overview of the intervention content is presented in Figure 2.

#### 2.4.3. Intervention Fidelity

To ensure consistency in the delivery of the intervention, teachers will be provided with standardized materials, including the FiTeens toolkit, structured lesson plans, student learning portfolio, intervention manual, and standardized PowerPoint presentations prepared for each lesson. Teachers will receive an initial introduction to the FiTeens digital tools and intervention procedures prior to implementation. Each lesson follows a predefined structure consisting of an introduction, main activity, and conclusion, which supports consistency across sessions and schools. Adherence to the intervention will be monitored through student-completed challenge diaries and regular reflection activities conducted at the beginning of each session, providing insight into student participation in assigned challenges. Although formal observation of teaching sessions is not included, the use of standardized materials, unified PowerPoint presentation formats for each lesson, and structured implementation procedures is intended to support intervention fidelity.

#### 2.4.4. Post-Intervention Phase

Post-intervention data collection is conducted at 1, 3 and 6 months after the intervention and included questionnaire completion and the use of an accelerometer and Polar M400 for seven consecutive days.

